#### Laboratory pre- and post-testing

In the laboratory, we will administer the short version of the Balance Evaluation Systems Test, MiniBESTest, a 14-item test of balance ability shown to be related to fall risk in people with PD [35, 36]. In addition, the following questionnaires will be administered: the Activities-specific Balance Confidence (ABC) Scale, the Falls Efficacy Scale International (FES-I) to assess fear of falling, the Parkinson’s Disease Quality of Life questionnaire (PDQ-39) to assess quality of life and the first 10 questions reflecting the Mobility domain for quality of life. Lastly, the Movement Disorders Society Universal Parkinson Disease Rating Scale motor subscale (MDS-UPDRS III) will be administered again at the post-intervention session as well as the Patient Global Impression of Change (PGIC), a one question measure on a seven point Likert scale in which the participant rates their perceived change [37] and the Clinical Global Impression of Change (CGIC) scale [37–39]. A blinded clinician ([name]) will review videos of the MDS-UPDRS Part III and provide the score for the CGIC.

#### Daily-life monitoring

For measurement of mobility in daily life, participants will wear Opal Instrumented Socks that are made of a thin elastic cloth and have inertial sensors embedded. When worn, the sensors are located on the dorsum of the foot with the battery above the lateral malleolus (Fig. 2). They will also wear an Opal sensor on a belt with the sensor placed over the lumbar area (Opal and Opal instrumented socks by APDM Wearable Technologies, a Clario company). Participants will put the sensors on in the morning and wear them for 8–10 h per day for 7 days. The sensors are taken off and placed in a charger each night. At the end of the 7 days, the sensors are returned by mail or picked-up from their home by a study team member.

**Fig. 2 Fig2:**
[figure not shown]
Instrumented socks with inertial sensors on top of foot (**A**) and battery on the side **B**

#### Primary outcome measure

To test our hypothesis that rehabilitation can improve turning performance, the primary outcome measure for this pilot study will be the change in variability (SD) of the number of steps to turn averaged over the 7 days of daily monitoring. Our previous studies showed that variability of the number of steps to turn was sensitive and specific to PD and related to falls in the elderly [30, 40].

*Secondary outcome measures* will be: 1) other daily-life gait and turning measures (Table 2), 2) daily life monitoring measures (Table 2), 3) clinical measures (Table 3), and 3) fall rate during 12 months after intervention.

#### Falls Tracking

After the post-testing session falls will be tracked prospectively for 12 months. Automated emails (via REDCap) will be sent every two weeks to ask if a fall(s) has occurred, and if there has been any change in medications or activity levels. If a participant responds YES to any of the questions, then a research assistant will follow-up with the participant for more details about the fall, change in medication or activity. If a fall has occurred, we will determine the severity and circumstances of the fall and whether it resulted in an injury or required medical intervention. A fall will be defined as “an event that results in coming to rest unintentionally on the ground or other lower level” [41].

### Statistical analysis

The primary outcome will be compared between the intervention and control groups after 6 weeks of participation in the trial. We will compare the two groups at the 6-week time point using analysis of covariance, controlling for individual baseline levels. Outcomes will be transformed to meet normality assumptions. Level of significance will be set at 0.05; however, the randomized group differences will be reported (regardless of significance), along with their corresponding 95% confidence intervals to inform power and sample size for future trials. Analyses will first be conducted without other covariates, then followed by models adding covariates (such as age, gender, disease duration, freezing of gait) to determine any attenuation or increase of group effect sizes. The change in outcomes from baseline to 6 weeks will be compared between groups via t-tests (no covariates), or linear regression (with covariates such as severity of disease, age, gender, freezing of gait) as well. The strategy for analysis of secondary outcomes will proceed similarly, although may require other types of regression models (logistic, ordinal, Poisson, etc.), depending on their measurement characteristics.

The effect sizes from models fit for this pilot study will be used to determine number of subjects required for a future clinical trial. Those effects sizes cannot be determined at this point, but as an example, we investigated sample size requirements under a variety of scenarios. As an example, if difference between groups after intervention is 0.50 SD after controlling for baseline levels, and baseline levels account for 20% of variability in outcome at follow-up, then we would require 52 patients per arm (104 total) in a two-group, parallel arm randomized trial to achieve 80% power when alpha = 0.05. As we intend to use this study to power future, larger study and investigate the efficacy of TURN-IT on mobility in daily life, we plan on continuing recruitment until we reach the abovementioned sample size and accommodate for any drop-out. No interim analysis on the primary outcome will be done as the size of the study is relatively small and due to the known minimal risk of exercise intervention for PD.

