### Randomization for Rigor

After completing baseline testing, each participant will receive their group assignment from the unblinded research assistant. To maintain rigor of study design, subjects will be randomized into either the TURN-IT or Control groups via a blocked random allocation strategy. Randomization will use a blocked stratification design to balance the distribution of ‘PD severity’ (Hoehn and Yahr II or III-IV and freezing of gait status) between arms. The blocking will help ensure equal numbers in the two arms, and we will vary block sizes (2, 4, 6 or 8) to help avoid selection bias. All subjects will agree not to change their exercise activities or anti-Parkinson medication during the pre-intervention week of baseline testing, the 6-week intervention/control period or week of post-intervention week testing. The study biostatistician ([name]) will implement the randomization method in our Research Electronic Data Capture (REDCap) database [34].

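### Randomisation is stratified by Hoehn and Yahr stage and freezing of gait, but the lead ANCOVA omits both, which costs some precision if the strata are prognostic

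*Protocol article*

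**What the plan says.** Under Randomization for Rigor: "Randomization will use a blocked stratification design to balance the distribution of" PD severity, which is spelled out as "Hoehn and Yahr II or III-IV and freezing of gait status) between arms". Two factors with two levels each give four strata. Blocks vary in size: "we will vary block sizes (2, 4, 6 or 8) to help avoid selection bias".

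Under Statistical analysis, the primary comparison is: "We will compare the two groups at the 6-week time point using analysis of covariance, controlling for individual baseline levels". The order of models is then fixed: "Analyses will first be conducted without other covariates, then followed by models adding covariates (such as age, gender, disease duration, freezing of gait" and so on). The stated purpose of the later models is "to determine any attenuation or increase of group effect sizes".

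A further analysis compares change from baseline by t-test or by "linear regression (with covariates such as severity of disease, age, gender, freezing of gait) as well".

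The same section sets the significance level ("Level of significance will be set at 0.05") and says that group differences will be reported with 95% confidence intervals, significant or not, to help plan later trials.

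**The concern.** Blocking within strata makes the arms nearly equal on Hoehn and Yahr group and freezing status, so variation between strata is largely removed from the difference between arms. An ANCOVA without these factors still counts that variation as residual error. Its standard error then describes a trial randomised without stratification, and is larger than the real sampling error of the estimate.

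The loss is in precision: a wider interval than the design earned, a test that rejects less often than 5% under the null, and some lost power. In a pilot of 60 whose intervals and effect sizes are a stated product for planning the next trial, that is worth avoiding when the remedy is nearly free.

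**Working it through.** **Stated figures.** A two-sample t-test with 30 per arm and two-sided alpha 0.05 (noncentral t) gives 81.5% power at 0.75 SD, 96.8% at 1 SD and 99.7% at 1.25 SD. These match the Sample Size section (81.5%, 96.8%, > 99%). They use no covariates, so this point does not affect them. The future-trial example also reproduces: with 0.50 SD and baseline R-squared 0.20, 52 per arm gives 80.6% and 51 gives 79.8%.

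**Inputs from the article.** N = 60, 1:1 allocation, four strata, blocks of 2, 4, 6 or 8, alpha 0.05. Baseline R-squared 0.20 is taken from the future-trial example, since none is given for this outcome.

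**Assumptions.** Each factor has prevalence p of 20% to 50%. The two factors are independent of each other and of baseline. Each shifts the outcome by g = 0, 0.3, 0.5 or 0.7 SD, where the SD is that of the outcome within a stratum.

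**Approximation by hand.** With strata in the model, residual variance is 0.80. Without them it is 0.80 + 2g²p(1 − p). The standard error of the difference is about √(variance × 4/60).
- p = 40%, g = 0.5: 0.80 + 2 × 0.25 × 0.24 = 0.92. Model SE ≈ √(0.92/15) = 0.248, against √(0.80/15) = 0.231 if balance were perfect.
- p = 50%, g = 0.7: 0.80 + 2 × 0.49 × 0.25 = 1.045. Model SE ≈ 0.264 against 0.231.

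Incomplete last blocks leave a little imbalance, so the true SE lies slightly above 0.231.

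**Simulation.** 20,000 trials per row. Model A is arm + baseline. Model B adds the two factors. Power is at a difference of 0.75 SD, and losses were computed before rounding. Monte Carlo error is about 0.15 points for type I error and 0.25 for power.

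| p | g | Model SE, A | True SE, A | Type I, A / B | Power, A / B | Points lost |
|---|---|---|---|---|---|---|
| 20% | 0 | 0.232 | 0.232 | 4.9% / 5.0% | 88.5% / 88.3% | −0.2 |
| 20% | 0.3 | 0.236 | 0.233 | 4.6% / 5.0% | 87.8% / 88.4% | 0.6 |
| 20% | 0.5 | 0.244 | 0.236 | 4.4% / 5.0% | 86.4% / 88.5% | 2.1 |
| 20% | 0.7 | 0.254 | 0.240 | 3.9% / 5.4% | 83.7% / 87.9% | 4.2 |
| 40% | 0.5 | 0.249 | 0.236 | 3.9% / 5.2% | 85.2% / 88.4% | 3.2 |
| 50% | 0 | 0.232 | 0.234 | 5.2% / 5.2% | 88.4% / 88.4% | 0.0 |
| 50% | 0.3 | 0.239 | 0.235 | 4.5% / 5.0% | 87.6% / 88.6% | 1.0 |
| 50% | 0.5 | 0.250 | 0.234 | 3.7% / 5.0% | 85.3% / 88.6% | 3.2 |
| 50% | 0.7 | 0.266 | 0.235 | 2.7% / 4.9% | 81.8% / 88.6% | 6.8 |

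A separate run of the same design put the 0.7 SD case at about 2.3% to 3.5% type I error and 5 to 7 points of power. Taking both runs together, I use 2.3% to 3.9% and 4 to 7 points.

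**Second parametrisation.** Let the strata explain 10%, 20% or 30% of the variance left after baseline, at 40% prevalence (10,000 trials each). Type I error without strata is then 4.1%, 3.2% and 2.1%, against about 5% with them. Power at 0.75 SD rises from 89.3% to 91.0%, 91.0% to 94.3% and 92.1% to 96.6% when they are added.

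**The case against.** A reader might infer that the lead test is invalid or the treatment effect biased. Neither follows. Randomisation protects the estimate, and the error in the standard error is on the safe side: type I error stays at or below about 5% and the interval over-covers.

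A reader might also infer that the plan never adjusts for severity. That goes too far. Freezing of gait is an example covariate in the follow-on ANCOVA models. Severity of disease and freezing of gait are both examples in the change-score regression, and the randomisation section uses severity as its label for the stratification factors. Both lists are open, so absence of Hoehn and Yahr from one of them is not exclusion. What stands is narrower: the lead model omits both factors, and nothing commits both to any named model.

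The size can fairly be disputed. The article gives no prognostic effect and no prevalence, and the loss is nil if the strata add nothing beyond baseline. A single figure would not be supportable; only a range is.

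The link to the next trial is also looser than it first appears. Adjusted models will be available for planning, and an interval that is somewhat wide errs towards caution.

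Finally, the aim of seeing whether effect sizes change on adjustment describes follow-on models. Removing it would be a preference, not a correction.

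The point cannot be set aside as detail left to an unseen analysis plan, because the article states the order of models explicitly.

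**Conclusion.** The concern holds as a matter of precision, not validity. The direction is certain whenever the strata predict outcome beyond baseline: the reported standard error is too large and the test conservative. The size is conditional on the assumptions listed in the working. Power lost at 0.75 SD is about 0 for non-prognostic strata, up to 1 point at 0.3 SD per factor, 2 to 3 points at 0.5 SD and 4 to 7 points at 0.7 SD. Type I error is about 3.7% to 4.4% at 0.5 SD and 2.3% to 3.9% at 0.7 SD. The change should be made because it is nearly free and the intervals have a stated planning use.

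**What to change.** Define the primary model as ANCOVA of the 6-week value on arm, baseline value, Hoehn and Yahr group (II versus III-IV) and freezing of gait status, with the factors coded as used for randomisation. Keep the baseline-only ANCOVA as a sensitivity analysis. Include the same two factors in models for continuous secondary outcomes. In logistic or ordinal models, include them only where cell counts allow: at 60 participants sparse cells can make the fit unstable, and adjustment changes the odds ratio being estimated. The follow-on models with age, gender and disease duration can stay as they are.

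The cost is a line of text and two degrees of freedom (57 to 55 residual). When the strata had no effect, the simulated power cost was 0 to about 0.25 points. Both factors are already known before randomisation, so no new data are needed.

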## Discussion

The TURN-IT study, a randomized controlled clinical trial, is designed to test whether a novel turning focused rehabilitation intervention can improve turns in daily life in people with PD who have a history of falls. There are several novel aspects to our study including a comprehensive turning-focused intervention that is tailored to each underlying constraint that impairs turning in people with PD. Further, our outcome measure of turning quality during seven days of daily life is cutting edge and has implications for determining real-life changes after rehabilitation. The ultimate goal of this rehabilitation intervention is to improve how patients turn in daily life and to reduce falls.

Previous work on turning rehabilitation is limited. The American Physical Therapy Association recently released the clinical practice guidelines (CPG) for physical therapy for PD [21]. This CPG is structured around 11 recommendations and turning is discussed within task-specific training, although only two studies were high quality and one was moderate quality. One high-quality study compared a turning training program using either a rotational treadmill or a turn-specific, training program and found that both the rotational treadmill program and turning-specific exercise group had greater turning improvement than the control program (seated stretching) [42]. The other high-quality study practiced turning in an aquatic setting and while they found improvements in the Timed Up and Go and Berg Balance scale, both of which include turning, quality of turning, itself, was not an outcome [43]. Another study of moderate quality used clock-stepping training as a cognitive movement strategy for turns and found that, compared to usual care, the turn training improved some measures of turning including speed and foot clearance but did not improve number of steps to turn [44].

There are a handful of other studies, not included in the CPG, that used different training approaches to improve turning. One study used augmented reality, visual cues for rehabilitation but found this approach did not help turning parameters and, in fact, worsened some [45]. Others have tried cueing with mixed results including a study that found unilateral auditory cueing and attentional strategies to prompt a turn with a head-first strategy did not improve axial movement deficits [46]. While the head-first strategy improved head-pelvic dissociation, it created other problems, including an exaggeration of the CoM shift to the inside of the turn. With cueing, turning became even more en-bloc with a decrease in separation of the head and pelvic rotations. Another small study focused on axial mobility to improve turns and showed improvements with a home-based exercise program [47]. The most recent Cochrane review of rehabilitation for PD summarizes studies showing improvements in gait speed but did not find rehabilitation studies to improve turning ability [48, 49]. We hypothesize that our intervention, which targets multiple underlying physiological constraints on turning performance, will improve daily life turns more than a singular intervention such as cueing.

An important aspect to this study is the focus on objective measures of turning in daily life as outcome measures. Our work and others has demonstrated the importance of home monitoring to detect deficits [50, 51] and this study will determine the role home monitoring of daily life as an outcome measure after rehabilitation. Leach et al. [52] also demonstrated the importance of continuous monitoring to measure turn quality, quantity and variability to prospectively determine fall risk in older adults.

The potential impact of effective turning rehabilitation for people with PD, and more generally in aging populations, may be profound. Falls are the most common reason for injuries in older individuals, and people with PD fall five times more than age-matched controls [9, 53]. Falls in the United States cost the economy an estimated 50 billion dollars in 2015 for both fatal and non-fatal falls in older adults [54]. In addition to the economic consequences, it has been show that falls can create fear of falling, which can restrict activity and negatively affect quality of life [55]. Turning is a task requiring control of dynamic balance that is impaired in many elderly, neurological, and orthopedic patients. Turning is often affected because it involves complex coordination of walking with dynamic balance control including an integration of multiple biomechanical, sensory and motor systems. Because turning is a dynamic balance skill that is critical for most functional activities, rehabilitation that can improve turning in daily life may improve independence, safety in daily activities and reduce falls.

## Data Availability

The data from this study will be made publicly available as supplementary materials in the publication.

## Abbreviations

ABC Scale: Activities-specific Balance Confidence Scale
ABC: Agility Boot Camp
ABC-C: Agility Boot Camp–Cognitive focus
APA: Anticipatory Postural Adjustments
APR: Automatic Postural Reaction
AWS: Amazon Web Service
CoM: Center of Mass
CGIC: Clinician Global Impression of Change
CPG: Clinical Practice Guidelines
FES-I: Falls Efficacy Scale International
IRB: Institutional Review Board
MoCA: Montreal Cognitive Assessment
MDS-UPDRS: Movement Disorders Society–Unified Parkinson’s Disease Rating Scale
NFOG-Q: New Freezing of Gait Questionnaire
OHSU: Oregon Health & Science University
PD: Parkinson’s Disease
PDQ-39: Parkinson’s Disease Questionnaire - 39
PGIC: Patient Global Impression of Change
REDCap: Research Electronic Data Capture
SD: Standard Deviation
TURN-IT: Turning Intervention
UE: Upper extremity
